### Sample Size and Power

The sample size calculation is based on examining the differences between treatment groups after 6 weeks on the primary outcome measure (OSW), while preserving adequate power for detecting the sub-grouping effect in hypothesis 3. In our preliminary study [29] we found a treatment effect following the traction intervention of 0.47, based on a mean between group difference of 6.4 points on the OSW with a sd of 13.7, and a correlation between baseline and follow-up OSW scores of *r *= 0.57. We believe our modification of the traction protocol in the present may improve the treatment effect. A sample size of 128 subjects would provide 80% to detect a slightly larger effect size (0.50). Adjustment for the baseline OSW score will improve power versus an unadjusted comparison of means [44]. Presuming a correlation between baseline and post-treatment OSW scores of 0.57, a sample size of 86 subjects would provide 80% power for the same treatment effect [44]. To preserve adequate power to examine the interaction effect related to the sub-grouping status in hypothesis 3, we inflated the sample size based on the size of the anticipated interaction effect relative to the overall treatment effect [45]. In our preliminary study, the magnitude the interaction effect was 1.07 sd between subjects receiving traction who were SG+ compared with subjects receiving EOTA only who were SG+, and was 0.71 sd between subjects receiving traction who were SG+ and those receiving traction who were SG-. If the sub-group effect size is presumed to be at least 1.0, no further sample size inflation would be required to maintain the same power as for the overall treatment effect, while a sub-group effect size of 0.71 would require an inflation of approximately 1.5 [45]. Inflating the sample size by 1.2 results in a sample size of 104 subjects. Recruiting 120 subjects (60 per group) allows for a drop-out rate of approximately 13%. Our sample size estimate would be under-powered if a large clustering effect due to subjects within clinical sites were present [46]. We are presuming that our use of standardized protocols will make any clustering effects negligible. If this presumption proves incorrect the study could be under-powered. Conversely, our sample size calculation accounts for adjustment for baseline OSW values. We will adjust for additional baseline co-variates which may increase power. A sample size of 120 subjects provides 80% power to detect a between-group difference in low back or leg pain rating of 1.0 points presuming a sd of 2.0, and a difference in the percentage of successful patients of 25% based on dichotomization of the global rating of change scale.

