### Preliminary Research to Identify a Sub-Group of Patients Likely to Benefit from Traction

As an initial step towards investigating if a more clinically-relevant traction protocol would result in larger treatment effects, and to explore if a specific sub-group of patients with LBP exists for whom evidence would support the use of traction, we conducted a randomized clinical trial [29]. The inclusion criteria for this trial were designed to provide a more homogeneous sample that reflected clinicians' perceptions of the appropriate sub-group of patients most likely to benefit from traction. The trial required patients to have symptoms distal to the buttock accompanied by clinical signs of nerve root irritation. Because we hypothesized that clinically important heterogeneity may exist even within this more narrowly-defined sample of patients, we secondarily examined additional baseline variables, nominated based on expert opinion and observations, for their potential to further define a traction sub-group. The trial randomized patients to one of two treatment groups, both of which received 6 weeks of treatment involving an extension-oriented treatment approach (EOTA) comprised of repeated end-range extension exercises and supplemented with manual therapy and education designed to facilitate centralization of the patient's symptoms. One group also received mechanical traction during the first two weeks of treatment, in addition to this extension-oriented approach (EOTA+traction). The traction protocol was designed to reflect common clinical practice [28] and was informed by expert clinical input [30]. The protocol used a high dosage of traction, with a sustained traction force ranging between 40%-60% of a patient's body weight, delivered for a maximum of 12 minutes during a treatment session. The delivery of traction was combined with concomitant use of the EOTA interventions designed to enhance centralization of symptoms. We provided this high-dose traction during the initial 2 weeks of traction to reflect the clinical perception that traction is most effective when delivered early in the course of treatment, followed by transition to exercise or other patient-directed activities [30].

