Analysis of the overall randomized trial results found a significant time x treatment interaction after 2 weeks, but not at the 6 week follow-up for the outcome of disability (Modified Oswestry questionnaire) (figure 1). The group receiving EOTA+traction experienced greater change after 2 weeks on the Oswestry questionnaire, however the magnitude of the treatment effect was at the margins of clinical significance [31] (mean difference = 7.2 points (95% CI: 0.13, 14.3)), and was no longer significant after 6 weeks. Our secondary analysis identified two baseline variables that significantly interacted with the treatment provided: the presence of peripheralization of symptoms with extension movement, and a positive crossed straight leg raise test. Analysis of the results using the presence of either of these two factors to preliminarily define a sub-group of likely traction responders (table 1) demonstrated a significant time x treatment x sub-group status, 3-way interaction at both the 2- and 6-week follow-up (figure 2). The nature of this interaction indicated that patients who met the preliminary sub-grouping criteria and received traction experienced greater change in disability across time than those who did not meet the sub-grouping criteria and received traction, or those who met the criteria but did not receive traction (figure 2). The presence of this interaction suggests the sub-grouping criteria identified in this preliminary study may represent an effect modifier specific to the use of lumbar traction (i.e., the response to lumbar traction is expected to differ based on sub-grouping status) [32]. Additional research in different patient samples is needed to validate or refute this preliminary finding [33].

**Table 1 T1:** Definition of preliminary criteria to define a sub-group of patients likely to benefit from traction.

Criterion	Definition
**1**. Peripheralization with extension movement	Presence of peripheralization with at least one of the following extension movements during the baseline examination: single extension standing, repeated extension standing, sustained extension prone (prone on elbows), or repeated extension prone (prone press-ups). Peripheralization is judged to have occurred if a pain or paresthesia moves distally away from the spine toward the periphery, or paresthesia or a neurological sign is worsened or produced during or after the movement [48].

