### Data Analysis

Intention-to-treat principles will be applied to all analyses, with all subjects analyzed with the group to which they were randomized regardless of compliance with treatment. Hypotheses 1 and 2 relate to determining the overall effectiveness of adding traction to an EOTA intervention. Linear mixed models with repeated measures will be used to analyze overall treatment effectiveness. The treating physical therapist and physical therapy clinic will be modeled as random effects. Covariates, treatment group, and treatment group by time interaction will modeled as fixed effects. The treatment group by time interaction effect will be used to examine hypotheses 1 and 2 related to the effectiveness of adding traction to an EOTA intervention. Treatment effect sizes with 95% confidence intervals will be calculated for each follow-up time point. The third hypothesis, examining effectiveness of adding traction to an EOTA intervention based on subjects' status on the preliminary sub-grouping criteria, will be examined with similar procedures with the inclusion of a 3-way, time by group by sub-grouping status interaction term. Statistical significance will be based on an alpha level of 0.05 for all analyses.

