
## Discussion

This study will examine the effectiveness of adding a standardized protocol of lumbar mechanical traction to an extension-oriented treatment approach for individuals with LBP and nerve root irritation who are receiving non-surgical care. The study will further examine if the addition of the traction protocol is particularly beneficial in a sub-group of subjects defined by the presence of clinical examination factors identified in preliminary research. The study will examine the overall effect of the treatment received, and the interaction between treatment received and the sub-group status. This is the recommended strategy for determining if treatment effects differ across sub-groups [47]. The sample size has been adjusted to preserve adequate power for the analysis of the sub-grouping interaction effect [45]. There is currently a lack of evidence to inform clinical decision-making for the non-surgical management of LBP and nerve root irritation, even though a period of non-surgical management is recommended for most patients. The overall goal of this study is to provide evidence that can improve decision-making for these patients.

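### The interaction effects used to size hypothesis 3 come from the 64 patients in whom the criteria were selected, and the adequate-power statement holds only for interactions of about 0.9 sd or more

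*Protocol article*

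**What the plan says.** The Background section on preliminary research describes how the criteria arose. Within the earlier randomised trial, "we secondarily examined additional baseline variables, nominated based on expert opinion and observations, for their potential to further define a traction sub-group". Then: "Our secondary analysis identified two baseline variables that significantly interacted with the treatment provided". The two variables were joined by an either/or rule, and the three-way interaction for that rule was reported from the same trial. The Randomization section gives that trial's size as 64 patients, 32 of them SG+.

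Sample Size and Power takes 1.07 sd (SG+ with traction against SG+ without) and 0.71 sd (SG+ with traction against SG- with traction) from that trial as the anticipated interaction. It reasons that "If the sub-group effect size is presumed to be at least 1.0, no further sample size inflation would be required", gives a factor of about 1.5 for an effect of 0.71, and applies 1.2. This leads to 104 analysed and 120 recruited. The only cause of low power that the section names is clustering.

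The Discussion concludes: "The sample size has been adjusted to preserve adequate power for the analysis of the sub-grouping interaction effect". Data Analysis tests hypothesis 3 with a three-way interaction term and adds: "Statistical significance will be based on an alpha level of 0.05 for all analyses".

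**The concern.** When variables are kept because their interaction reached significance, and the rule built from them is evaluated in the same patients, the estimated effect is too large on average. The article calls the sub-group finding preliminary and asks for confirmation in new patients, but the sizing uses the two estimates without shrinkage, interval or caveat.

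The new trial is the test of those criteria. If the true interaction is appreciably smaller than the pilot suggested, the trial has a substantial chance of a non-significant result. A reader who relies on the statement that power was preserved could take that result as evidence against the sub-group when it is only uninformative.

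**Working it through.** **Inputs.** All are from the protocol article: overall effect 0.50 sd, 80% power, r = 0.57, inflation 1.2, 104 analysed, 120 recruited with 60 per group (Sample Size and Power); 50% SG+ expected (Randomization); alpha 0.05 (Data Analysis). Assumptions: two-sided test, four equal cells, no clustering, a single follow-up adjusted for baseline.

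**The plan's own chain reproduces.**
- "based on a mean between group difference of 6.4 points on the OSW with a sd of 13.7": 6.4 / 13.7 = 0.47.
- Two-sample t-test at 0.50 sd: 128 in total.
- "Presuming a correlation between baseline and post-treatment OSW scores of 0.57, a sample size of 86 subjects would provide 80% power": 128 × (1 − 0.57²) = 128 × 0.675 = 86.4, so about 86.
- 86 × 1.2 = 103.2, taken as 104. 1 − 104/120 = 13.3% drop-out.

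**What the 1.2 inflation stands for.** With four equal cells, an interaction δ needs 4 × (0.50/δ)² times the sample size of the overall effect.
- δ = 1.0 gives 1.0, which agrees with the article.
- Setting the factor to 1.2 gives δ = 2 × 0.50 / √1.2 = 0.91 sd.
- δ = 0.71 gives 1.98, not the stated 1.5. This is a separate matter and the point does not rest on it.

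**Detectable interaction with 104 analysed (26 per cell).**
- SE = √(4 × 0.675 / 26) = 0.322 sd.
- 80% detectable = (1.96 + 0.84) × 0.322 = 0.90 sd. 0.903 × 13.7 = 12.4 Oswestry points.
- With all 120 analysed (30 per cell), SE = √(4 × 0.675 / 30) = 0.300 sd.

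**Power for the interaction (t-test, N − 5 df).**

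| True interaction (sd) | Oswestry points | 104 analysed | 120 analysed |
|---|---|---|---|
| 1.00 | 13.7 | 87% | 91% |
| 0.90 | 12.3 | 79% | 84% |
| 0.71 | 9.7 | 59% | 65% |
| 0.60 | 8.2 | 45% | 51% |
| 0.50 | 6.9 | 34% | 38% |

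The 0.60 and 0.50 rows are assumed values, because the documents give no estimate corrected for selection.

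**Direction of the bias.** With 64 patients in four equal cells and the same baseline adjustment, SE = √(4 × 0.675 / 16) = 0.41 sd. Only estimates above 1.96 × 0.41 = 0.81 sd reach p < 0.05. For a single interaction, simulation gives a mean estimate, among those significant in the favourable direction, of 0.96 when the truth is 0, 1.04 when it is 0.50, 1.10 when it is 0.71 and 1.21 when it is 1.0. A significant pilot estimate near 1 sd therefore says little about the true size. The simulation shows direction only. The number of candidate variables and the intervals are not given, so the actual bias cannot be computed.

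**The case against.** The strongest reply is that the plan did not size on 1.0. It weighed 1.0 against 0.71 and applied 1.2, equivalent to about 0.91 sd. The pilot figures of 1.07 in SG+ and 0.47 overall imply 2 × 0.47 − 1.07 = −0.13 in SG-, hence a difference of effects of 1.20 sd. Against that, the design tolerates a shrinkage of about a quarter: power at 0.90 is 79%, or 84% with nobody lost. This stands, and the point must not be put as though 1.0 had set the sample size. But the article does not present the margin as an allowance for selection, and power is already about 59% at its own lower figure of 0.71.

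The candidates were nominated by experts rather than screened indiscriminately, and traction now runs for six weeks instead of two, which the authors think may enlarge the effect. Both are fair. They bear on how large the bias may be, not on whether the estimates come from the selection sample.

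Three stronger readings are tempting and not supported.
- A reader might infer that the pilot interaction is an artefact, or that a smaller one is the likely truth. The documents cannot show this. In simulations with no true interaction and an assumed 6 to 20 candidates, two factors passed in only about 1% to 9% of trials.
- A reader might treat the pilot figures as upper bounds. Bias on average is not a bound.
- A reader might infer that a null result will be read as refutation. No section says so. The article says only that research is needed to confirm or overturn the finding, and it promises 95% intervals for treatment effects at each follow-up.

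**Conclusion.** The point holds in limited form. The anticipated interaction effects were estimated in the patients who supplied the criteria and are likely too large on average, by an amount that the documents do not reveal. The statement that adequate power was preserved is right for interactions of about 0.9 sd (12.4 points) or more and not for smaller ones: about 59% at 0.71, 45% at 0.60 and 34% at 0.50 with 104 analysed, and 65%, 51% and 38% with all 120. These figures assume four equal cells, r = 0.57, two-sided 0.05 and no clustering; clustering could lower them, and further covariates could raise them. A null result could be misread; nothing written says that it will be.

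**What to change.** Keep 120 patients and the analysis model, and change the wording in three places.

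1. **Sample Size and Power:** say that 1.07 and 0.71 sd come from the sample in which the criteria were derived and are likely too large. State the interaction detectable with 80% power at 104 analysed (about 0.90 sd, 12.4 points) and the power over a shrunken range, for example 0.50 to 1.0 sd.
2. **Discussion:** limit the adequate-power statement to interactions of about 0.9 sd or more.
3. **Data Analysis:** state that hypothesis 3 is read from the estimate and 95% confidence interval of the difference in treatment effect between SG+ and SG-. A non-significant result is inconclusive unless the interval excludes a worthwhile interaction, whose size is stated in advance.

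No extra patients or data are needed. The cost is a less favourable stated power for hypothesis 3, and the need to commit beforehand to a worthwhile interaction size.

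### By the plan's own rule a sub-group interaction of 0.71 sd needs an inflation of about 2.0, not 1.5, and the 1.2 applied keeps 80% power only for interactions of about 0.9 sd or more

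*Protocol article*

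**What the plan says.** Sample Size and Power builds the sample size in steps.

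- Unadjusted: "A sample size of 128 subjects would provide 80% to detect a slightly larger effect size (0.50" (an effect of 0.50).
- Baseline-adjusted, with r = 0.57 assumed: "a sample size of 86 subjects would provide 80% power for the same treatment effect".
- Interaction: the total is inflated according to the size of the interaction relative to the overall effect. A sub-group effect of at least 1.0 is said to need no inflation, "while a sub-group effect size of 0.71 would require an inflation of approximately 1.5 [45" (citing reference 45).
- Factor used: "Inflating the sample size by 1.2 results in a sample size of 104 subjects". No reason is given for choosing 1.2. Recruitment of 120 then allows for about 13% dropout.

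The section reports two pilot values under the label of the interaction effect. One is 1.07 sd, for SG+ patients with traction against SG+ patients without. The other is 0.71 sd, for SG+ patients with traction against SG- patients with traction.

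The stated purpose is to keep adequate power for hypothesis 3. The Discussion repeats this without an effect size: "The sample size has been adjusted to preserve adequate power for the analysis of the sub-grouping interaction effect [45".

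**The concern.** The two inflation figures cannot come from one rule. If an interaction of 1.0 needs a factor of 1, the factor at 0.71 follows from the squared ratio, and that is well above 1.5. The plan then applies 1.2, which is below even its own figure for 0.71, and still says that power for the interaction is kept. The misstated factor makes the gap at 0.71 look like 1.2 against 1.5, when it is 1.2 against about 2.0.

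Hypothesis 3 is one of the trial's main aims, and the Background says that new data are needed to confirm or overturn the pilot sub-group. A reader of the result needs to know how large an interaction the trial could reliably detect. The article does not say.

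**Working it through.** **Inputs.** All are from Sample Size and Power unless noted.
- Overall effect 0.50; pilot effect 0.47 (6.4/13.7).
- r = 0.57, so 1 − r² = 0.6751.
- Power 80%.
- Evaluable N = 104; dropout about 13%.
- SG+ prevalence 50% (Randomization section: 32 of 64 in the pilot).
- Alpha 0.05 (Data Analysis). Sidedness is not stated; two-sided is assumed because it reproduces 128.

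**1. The plan's other figures reproduce.**
- Unadjusted: 2 × (1.96 + 0.842)² / 0.50² gives 63 per arm, or 126 in total. By the t distribution, 64 per arm (128) gives 80.1% power.
- Adjusted: 128 × 0.6751 = 86.4, stated as 86.
- Inflated: 86 × 1.2 = 103.2, stated as 104.
- Recruited: 104/0.87 = 119.5, stated as 120.

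**2. The inflation rule.** In sd units, the baseline-adjusted variance of the overall effect is 4(1 − r²)/N. A treatment-by-sub-group interaction is a difference of differences over four cells of N/4, so its variance is 16(1 − r²)/N, four times as large. The factor that keeps the same power for an interaction δ is 4 × (0.50/δ)².
- δ = 1.0: 4 × 0.25 = 1.0. This matches the plan and confirms the rule. Power at N = 86 is 80–81%.
- δ = 0.71: 4 × (0.50/0.71)² = **1.98**. The plan says about 1.5.
- δ = 0.71 with 0.47 as the overall effect: 4 × (0.47/0.71)² = 1.75.

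Reading 0.71 as a simple two-cell contrast gives a factor of about 0.98 (84 patients needed, against 86). Only unsquared ratios come near 1.5 (0.71/0.47 = 1.51; 1/0.71 = 1.41). A missing square is a possible explanation, not an established one.

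With the factor of 1.98, 80% power at 0.71 needs 86 × 1.98 ≈ 171 evaluable patients (168 by direct normal calculation), or about 196 recruited at 13% dropout.

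**3. What 104 evaluable patients deliver.** SE = √(16 × 0.6751/104) = 0.322. Power at 0.71 is Φ(0.71/0.322 − 1.96) = 59.6%, or 58.8% by t. The interaction detectable with 80% power is 2.802 × 0.322 = 0.90 sd (about 0.91 by t). At sd 13.7 that is 0.903 × 13.7 ≈ 12.4 Oswestry points.

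| Evaluable N | Power at 0.71 | at 0.80 | at 0.90 | at 1.0 |
|---|---|---|---|---|
| 86 (no inflation) | 51–52% | 61–62% | 71–72% | 80–81% |
| 104 (factor 1.2) | 59–60% | 69–70% | 79–80% | 87% |
| 120 (no dropout) | 65–66% | 75–76% | 85% | 91–92% |
| 129 (factor 1.5) | 68–69% | 78–79% | 87–88% | 93% |

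Ranges are t-based to normal. If SG+ prevalence were 40% or 30%, power at 0.71 with N = 104 would be 58% or 52%.

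**4. What 0.71 and 1.07 measure.** As described, each compares two of the four cells. With 26 per cell at N = 104, SE = √(0.6751 × 2/26) = 0.228. Power is then Φ(0.71/0.228 − 1.96), about 88%, for 0.71 and above 99% for 1.07.

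Suppose the pilot cells were balanced, so that 0.47 is the average of the SG+ and SG- treatment effects. This is an assumption. The SG- effect is then 2 × 0.47 − 1.07 = −0.13, and the interaction is 1.07 − (−0.13) = 1.20 sd. Power at N = 104 would be about 96%.

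**The case against.** The strongest reply is that the power shortfall comes from treating 0.71 as a difference of differences, which the article does not define it to be. The two values correspond to hypotheses 3b (1.07) and 3a (0.71). As two-cell contrasts both are well powered, and the interaction that the pilot figures imply, near 1.2 sd, is powered at about 96%. Taking 1.07 as the SG+ effect, power falls below 80% only if the SG- effect exceeds roughly 1.07 − 0.90 = 0.17 sd. This stands. A reader might infer that hypothesis 3 is underpowered outright, or that enrolment must rise, and the documents do not support either inference.

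It does not rescue the 1.5. The article itself calls 0.71 an interaction effect and puts it into an interaction inflation rule, and no reading tried gives 1.5 with the correct variance. Data Analysis also tests hypothesis 3 through a time by group by sub-group term, so the power of a two-cell contrast is not the power of the planned test.

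Further points have weight:
- The 1.5 determines nothing in the design, since 1.2 was used, and a careful reader can see that 1.2 is less than 1.5.
- Reference 45 was not available, so its tabulated factor could not be checked.
- The corrected value depends on whether 0.50 or 0.47 is the overall effect.
- Additional covariates, which the plan intends to use, may raise power somewhat.

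A reader might also expect a non-significant interaction to be taken as disproof of the sub-group. The article states no such rule, and it already plans effect sizes with 95% confidence intervals at each follow-up, so no request is made on that.

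**Conclusion.** The point holds as an error in a stated sizing figure and a power claim that is too broad. By the plan's own scaling, the factor for an interaction of 0.71 sd is about 2.0 with an overall effect of 0.50, or 1.75 with 0.47. With 104 evaluable patients, adequate interaction power is kept for interactions of about 0.9 sd or more and not below. Using the wrong label of interaction for the two pilot contrasts hides which quantity the trial was sized for.

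This rests on 50% SG+, 1:1 allocation, r = 0.57, two-sided 0.05, no clustering, and adjustment for baseline Oswestry score only. It does not establish that the trial is too small for the interaction it is likely to meet. That depends on the SG- treatment effect, which the article does not report.

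**What to change.** Change the text in Sample Size and Power and in the Discussion; enrolment stays at 120.

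1. Correct the factor at 0.71 from about 1.5 to about 2.0, stating that it assumes an overall effect of 0.50 and half the patients SG+.
2. State which contrast is powered: the treatment-by-sub-group interaction, as a difference of differences.
3. Label 1.07 and 0.71 as two-cell contrasts, not as interaction effects.
4. Replace the unqualified claim of adequate interaction power in both places with wording such as: *With 104 evaluable patients, r = 0.57 and two-sided alpha of 0.05, power is 80% for a treatment-by-sub-group interaction of about 0.9 sd (about 12.4 points at sd 13.7), 87% for 1.0 sd, and about 59% for 0.71 sd.*

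The cost is a few sentences and a less favourable stated power for smaller interactions. No design or analysis step changes.

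### The closing power statement for pain and global rating uses the 120 recruited rather than the 104 expected to be evaluable, and gives no baseline adjustment for pain

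*Protocol article*

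**What the plan says.** All the power figures stand in one paragraph of the protocol article, Sample Size and Power.

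- Unadjusted comparison on the Oswestry score: "A sample size of 128 subjects would provide 80% to detect a slightly larger effect size (0.50").
- With adjustment for baseline Oswestry at a correlation of 0.57, the requirement for the same effect falls to 86.
- Inflation for the subgroup interaction: "Inflating the sample size by 1.2 results in a sample size of 104 subjects".
- Recruitment: "Recruiting 120 subjects (60 per group) allows for a drop-out rate of approximately 13" per cent.
- Pain: "A sample size of 120 subjects provides 80% power to detect a between-group difference in low back or leg pain rating of 1.0 points". The standard deviation behind this is put at 2.0.
- Global rating: the same power and the same 120 are claimed for a 25-point difference in the share of patients counted as a success.

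The sentence just before the secondary claims says that further baseline covariates will be adjusted for and may increase power. It names none and gives no correlation for pain. The Data Analysis section adds: "Statistical significance will be based on an alpha level of 0.05 for all analyses".

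**The concern.** For the primary outcome the paragraph separates two numbers: 104 needed for analysis and 120 to be recruited so that 104 remain. The secondary claims are attached to 120, as though nobody drops out.

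The pain claim also concerns an effect of 1.0/2.0 = 0.50. The paragraph has already priced that effect at 128 subjects unadjusted, so 120 cannot give the same 80% on the same basis. If the pain figure is meant to be adjusted for baseline, the sentence does not say so, although the Oswestry calculation states both the adjustment and its correlation.

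What is at stake is how a null pain or global-rating result is read. Readers would take it to come from a comparison with 80% power, when the plan's own inputs may support less.

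**Working it through.** **Inputs.** From Sample Size and Power: pain difference 1.0, sd 2.0, 60 per arm recruited, 104 after dropout (52 per arm), 25-point difference in success. From Data Analysis: alpha 0.05. Sidedness is not stated. I take it as two-sided because the plan's 128 reproduces only that way.

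**Reproducing the plan's own figures (d = 0.50).**
- Two-sample t-test, 64 per arm: power 80.1%, so N = 128, as stated. The normal approximation gives 63 per arm, N = 126.
- Baseline adjustment multiplies N by 1 − r²: 128 × (1 − 0.57²) = 128 × 0.6751 = 86.4, matching 86.
- 86 × 1.2 = 103.2, matching 104. Dropout allowed: 1 − 104/120 = 13.3%.

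**Pain, unadjusted.** Normal approximation: power = Φ(d√(n/2) − 1.96), with n per arm.
- n = 60: 0.5 × √30 = 2.739; Φ(0.779) = 78.2%. Noncentral t: 77.5%.
- n = 52: 0.5 × √26 = 2.550; Φ(0.590) = 72.2%. Noncentral t: 71.4%.

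Difference detectable with 80% power: 2.0 × (1.960 + 0.842) × √(2/n).
- n = 60: 1.02 points.
- n = 52: 1.10 points.

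**Pain, adjusted for baseline pain.** Replace the sd by 2.0 × √(1 − r²). The plan gives no r for pain, so these values are assumptions (power by noncentral t):

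| Evaluable | r = 0 | r = 0.3 | r = 0.5 | r = 0.57 |
|---|---|---|---|---|
| 120 | 77.5% | 81.3% | 88.0% | 91.1% |
| 104 | 71.4% | 75.4% | 83.0% | 86.7% |

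Correlation needed for 80%:
- At 120: √(1 − 120/128) = 0.25.
- At 104: √(1 − 104/128) = 0.433. A search in steps of 0.01 with the t-test gives 0.44.

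**Global rating, 25-point difference.** With p̄ the mean of the two rates, power = Φ{[0.25√n − 1.96√(2p̄(1 − p̄))] / √(p₁(1 − p₁) + p₂(1 − p₂))}, without continuity correction. Control rates are assumed, since none is stated:

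| Control v traction | 60 per arm | 52 per arm |
|---|---|---|
| 10% v 35% | 91.7% | 87.4% |
| 20% v 45% | 84.1% | 78.5% |
| 30% v 55% | 79.9% | 73.9% |
| 37.5% v 62.5% | 78.9% | 72.9% |
| 50% v 75% | 81.6% | 75.7% |
| 60% v 85% | 87.6% | 82.4% |
| 65% v 90% | 91.7% | 87.4% |

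The lowest value is at mid-range rates. The stated 80% therefore reproduces at 120 to within about one point at worst, and at 104 it depends on the control rate.

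**The case against.** The strongest reply is that the pain figure may be an adjusted one. The model includes covariates, the preceding sentence promises further baseline adjustment, and pain is measured at baseline. A correlation of about 0.25 would give 80% at 120 and about 0.44 would give it at 104. At the Oswestry value of 0.57, applied to pain as an assumption, power at 104 would be about 87%. This stands to the extent that a real shortfall cannot be asserted. It does not rescue the sentence, which names neither an adjustment nor a correlation for pain.

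Three stronger readings are tempting, and the document does not support them.
- A reader might infer that 120 patients plainly fail to deliver 80% for pain. With all 120 evaluable the gap is 2 to 2.5 percentage points, or 1.02 points detectable against 1.0, which is close to rounding.
- A reader might infer that both secondary claims are wrong. The global-rating claim reproduces at 120.
- A reader might infer that the trial will miss a true 1.0-point pain effect nearly 29% of the time. That holds only for an unadjusted test with the full dropout allowance used up.

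One could also argue for a one-sided test, which gives about 81-82% for pain at 104. But one-sided testing would need only about 100 subjects for effect size 0.50, so it cannot be the basis of the plan's 128.

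Finally, these are secondary outcomes, and the plan promises effect sizes with 95% confidence intervals at each follow-up, which limits the misreading of a null result. That bears on how much the point matters, not on whether the statement is right.

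**Conclusion.** The point holds in a limited form. The secondary power statement uses the recruited number where the plan's own working number is 104, and the pain claim does not state its basis.

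For pain, two-sided and unadjusted, power is about 78% with no dropout. That is a small gap, but still inconsistent with the paragraph's own 128. Power is about 71-72% at 104, with about 1.1 points detectable at 80%. The shortfall disappears if baseline pain is adjusted for and correlates with follow-up at about 0.44 or more, which the document neither states nor excludes.

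For the global rating, the claim is sound at 120. At 104, power is about 73-87% over assumed control rates of 10-65%, lowest in the middle of that range and without continuity correction.

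The primary Oswestry calculation, which does allow for dropout, is unaffected.

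**What to change.** Restate the closing sentence on 104 evaluable subjects.

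- **Pain:** either report about 71-72% power for 1.0 point unadjusted (80% for about 1.1 points), or report 80% for 1.0 point with baseline pain named as a covariate and an assumed baseline to follow-up correlation of at least about 0.44. The second option is preferable if that correlation can be supported, since baseline pain is already collected.
- **Global rating:** give the assumed control success rate and the power at 52 per arm that follows from it. A narrow range should not be written in without that rate.

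The cost is a change of text and, possibly, a less favourable stated power. Recruitment, the primary sample size and data collection stay as they are.
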